**Methods/design:**

We present a prospective, double blinded, clinical trial comparing two groups of patients with oral anticoagulants: one group was administered tetanus-diphtheria vaccine by intramuscular injection, while the other was administered the same vaccine by subcutaneous injection. Allocation to each group was randomized and the duration of the study was six years.

Study population: all patients treated with oral anticoagulants, who had been administered with at least one dose of vaccine, at 15 Health Centres in Vigo (Spain), and who agreed to participate in the study. The sample size was 115 patients in each group. The main variables for the safety analysis were the measurement of the brachial diameter, the appearance of basic injuries at the vaccine administration site, the appearance of pain and systemic reactions. The variable used for the efficacy analysis was a significant increase in the titres of anti-tetanus toxoid antibodies.

An Intention-to-treat analysis will be performed. Details will be classified according to the administration route, while within each group a 3-tiered stratification will be defined by the administered number of doses. As a measure of association, relative risk will be estimated; the reduction of relative risk will also measured. For safety and to control the confounder effect, a logistic regression analysis will be carried out. As a measure of impact the reduction of absolute risk in relation to the total number of patients to be treated and the Number Needed to Treat will be estimated.

CONSORT 2010 guidelines were applied for reporting parallel group randomised trials.

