### Sample size

Assuming that for the IM route the percentage of local side effects is 30% [11, 15, 16] and expecting an increase of 18% [15] in local secondary effects for the alternative route (SC), using a bilateral approach, with a 95% confidence interval, a beta risk of 0.20 requires 115 patients in each group. Taking into account the possible 15% loss in information, the final sample size was 135 patients in each group. With this sample size, it was estimated that a 3 UI/ml mean difference in antibody levels could be detected.

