### Variables

The main analytical safety variables were:Measurement of the brachial perimeter in centimetres.Appearance of basic injuries (redness, swelling, heat, granulomas, haematoma) in the area of administration of the vaccine, axillary nodes, and the appearance of pain measured with the visual analogue pain scale.The emergence of general symptoms (fever, malaise, headache, weakness, arthralgias).The appearance of any serious adverse effect: one that was fatal or posed danger to patient’ life, ended in disabilities or required hospitalization.

For each route of administration, the main variable used in the efficacy analysis was the increase in anti-tetanus antibodies following vaccination.

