### Statistical analysis

Descriptive, statistical analysis will be used to classify the data into two groups, according to the route of administration, while within each group a 3-tiered stratification will be defined by the administered number of doses. The quantitative data will be summarized by estimating the arithmetic mean and median as measures of central tendency, as well as the standard deviation as a measure of dispersion. For qualitative variables, proportions with 95% confidence intervals will be estimated.

After checking the conditions of application and assuming an alpha error of 0.05, the Chi-squared test will be used to determine the statistical differences between the qualitative variables in the two study groups. Prior checking of all the criteria for application will be carried out before the Student’s-t test (0.05 alpha) is used to examine the levels of significance in the differences in quantitative variables for independent data. If the conditions of application were not met, the non-parametric Mann–Whitney U test will be used. The Student’s t test for paired data will be employed for paired quantitative variables.

As an association measurement, relative risk will be estimated with a 95% confidence limit, according to the method of Mantel and Fleiss. In addition, as a further association measurement, relative risk reduction will be calculated with a 95% confidence interval. For the safety study and to control the effect of different confounding covariables, a logistic regression analysis will be simultaneously performed.

As a measurement of impact, the reduction of absolute risk (RAR) and the Number of patients Needed to be Treated (NNT) to prevent an event will be calculated with 95% confidence intervals.

An Intention-to-treat (ITT) analysis will be carried out, even when it was highly or totally improbable that crossing occurs within groups, because this intervention is predictably limited to a particular moment.

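### The between-route antibody comparison is valid but adjusts for neither baseline titre nor randomised dose tier, and the efficacy endpoint, its detectable difference and the timing of the first sample need tidying

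*Protocol article*

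**What the plan says.** - **Endpoint.** Under Variables, for each route, "the main variable used in the efficacy analysis was the increase in anti-tetanus antibodies following vaccination". The abstract (Methods/design) words it differently: "The variable used for the efficacy analysis was a significant increase in the titres of anti-tetanus toxoid antibodies". It gives no threshold and does not say what the word significant refers to.
- **Between-group test.** Under Statistical analysis, Student's t-test "is used to examine the levels of significance in the differences in quantitative variables for independent data", with the Mann-Whitney U test if its conditions fail. Separately, a t "test for paired data will be employed for paired quantitative variables".
- **Adjustment.** The same section assigns logistic regression with covariates to the safety study. No adjusted model is stated for antibodies. Dose tiers appear there only in the descriptive classification.
- **Design.** Allocation and masking stratifies by one, two or three doses, to control confounding by number of doses. Within a tier, randomisation is simple.
- **Data.** Interventions has antibody measured at the first visit and 30 days after the final dose. One sentence draws blood and then vaccinates; a later one appears to put the first measurement after vaccination.
- **Size.** Under Sample size, "using a bilateral approach, with a 95% confidence interval, a beta risk of 0.20 requires 115 patients in each group", based on local side effects. For antibodies, "it was estimated that a 3 UI/ml mean difference in antibody levels could be detected", with no SD.

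**The concern.** The trial aims to show that the intramuscular route is more efficacious as well as safer, and the efficacy half of that claim rests on one comparison of antibody response. Patients range from never vaccinated to due a booster, so baseline titres can be expected to differ between patients and between dose tiers. A test on the increase does use the baseline, but it fixes the baseline coefficient at 1 whatever the data show, and it leaves differences between tiers in the error term. Simple randomisation within tiers does not force balance between routes, so the design alone does not deal with tier.

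What is at stake is precision: a real difference between routes could be missed although the same patients and samples would show it under an adjusted analysis. This matters in a trial whose inclusion period had to be extended from 24 to 72 months to reach its sample size (Data collection).

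Three loose ends affect the same comparison: what the abstract's efficacy variable is, what SD lies behind 3 UI/ml, and whether the first titre is a true baseline.

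**Working it through.** **1. The plan's own sample size.** Inputs from Sample size: 30% against 48% (18 points higher), two-sided 0.05, power 0.80. The pooled proportion is 0.39.

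n = [1.960·√(2·0.39·0.61) + 0.842·√(0.30·0.70 + 0.48·0.52)]² / 0.18² = 114.1, so 115 per group. This reproduces the stated figure. For loss, 115/0.85 = 135.3, against 135 stated. Both figures concern local side effects, not antibodies.

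**2. The 3 UI/ml statement.** It cannot be reproduced without an SD. Solving backwards at 80% power, two-sided 0.05:

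- SD = 3 / [(1.960 + 0.842)·√(2/115)] = 8.12 UI/ml at 115 per group
- SD = 8.80 UI/ml at 135 per group

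**3. Change score against ANCOVA.** Assumptions, since the documents give none of these: baseline SD is 1, later SD is k, and the correlation is r.

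- Change-score variance: k² + 1 − 2rk
- ANCOVA variance: k²(1 − r²)
- Difference: (1 − rk)², which is never negative and is zero when the slope rk equals 1

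With k = 1 the ratio of change score to ANCOVA is 2(1 − r)/(1 − r²) = 2/(1 + r). Suppose 3 UI/ml is what the change score detects with 80% power at 115 per group (SD of change 8.12):

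| r (k = 1) | variance ratio | ANCOVA power, 115 per group | n per group for 80% | detectable difference (UI/ml) |
|---|---|---|---|---|
| 0.2 | 1.67 | 0.951 | 69 | 2.32 |
| 0.5 | 1.33 | 0.899 | 87 | 2.60 |
| 0.9 | 1.05 | 0.820 | 110 | 2.92 |

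With unequal SDs:

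- k = 2: 4.2/3.84 = 1.09 at r = 0.2; 3/3 = 1.00 at r = 0.5
- k = 4: 15.4/15.36 = 1.00 at r = 0.2; 13/12 = 1.08 at r = 0.5; 10.6/5.76 = 1.84 at r = 0.8

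So the ratio runs from 1.00 upwards, and the documents do not say where in the range this trial lies. The algebra holds on whichever scale the increase is taken. It covers baseline only: tier sizes and tier differences are not given, so no figure is offered for the tier adjustment.

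**4. Scale.** No scale is stated, but arithmetic means and a difference in UI/ml point to untransformed values. In simulations with assumed log-normal titres (log SD 0.8 to 1.5, 115 per group, a ratio detectable with 80% power on the log scale), the raw t-test had about 67% down to 42–43% power. Mann-Whitney, the plan's fallback, had about 76–79%. These runs compared titres, not increases.

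**5. Endpoint wordings.** Under randomisation the expected baseline is the same in both arms. The expected difference in mean levels (Sample size) therefore equals the expected difference in mean increases (Variables). The abstract's wording is the odd one out: read as a responder outcome, it would lead to chi-squared, relative risk and NNT instead of a comparison of means.

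**The case against.** The strongest reply is that nothing here is invalid. Under 1:1 randomisation an unadjusted comparison of increases is unbiased for route. The choice of a more efficient model is often left to an analysis plan, which is not shown and could add one. The Statistical analysis section is general and never names antibodies. All of this stands, and it limits the point to efficiency. It does not remove it: the section states which tests serve quantitative variables and which study gets adjustment, and the main efficacy variable is quantitative.

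Stronger readings are tempting but not supported:

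- *Three conflicting endpoints.* A reader might count three from the abstract, Sample size and Variables. The last two can describe the same contrast (step 5), so the real ambiguity is the abstract's.
- *Paired tests used to compare routes.* The plan gives the paired test to paired variables and a separate test to group differences. It does not offer the former as the route comparison.
- *A large loss from skewness.* The fall to about 42–43% is for a raw t-test that the plan would replace if its conditions fail, and the fallback recovers most of the loss. What remains is that Mann-Whitney does not estimate the 3 UI/ml mean difference and adjusts for neither baseline nor tier.
- *A fixed loss of a third or more.* The ratios 1.67 and 1.33 need equal SDs before and after vaccination, which is not a neutral assumption for raw titres around immunisation.

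On the first sample, the explicit sequence is blood and then vaccine, so the later sentence may be loose wording. It still needs reconciling, because every increase depends on it.

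**Conclusion.** The point holds as one of efficiency and clarity. The stated efficacy comparison is valid but uses neither the baseline titre as a covariate nor the dose tier used in randomisation, while adjustment is reserved for safety. Adjusting for baseline costs essentially nothing in large samples. If the change score has 80% power, equal SDs imply 82% (r = 0.9) to 95% (r = 0.2) with adjustment. The gain vanishes when the slope of the later titre on baseline is 1. These figures rest on an assumed r and SD ratio; the documents supply neither.

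Three smaller points stand on the text alone: the abstract's efficacy variable is undefined, the 3 UI/ml claim has no SD and cannot be checked, and Interventions gives two orders for the first sample and first dose. None of them affects the 115 per group, which reproduces.

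**What to change.** - Compare log antibody titre 30 days after the final dose between routes by ANCOVA, with log baseline titre and randomised dose tier as covariates. Report the geometric mean ratio with its 95% CI. This would replace the choice between t-test and Mann-Whitney for this endpoint.
- Align the abstract with the continuous endpoint under Variables.
- State the SD behind 3 UI/ml (about 8.1 UI/ml if it means 115 per group and 80% power, 8.8 at 135), or restate the detectable effect as a ratio on the log scale.
- Reconcile the two sentences in Interventions on the order of first sample and first dose, so that the covariate is clearly a baseline.

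The cost is wording only: no new patients, visits or samples. The one drawback is that the result is a ratio of titres in place of a difference in UI/ml.

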### Statistical analysis

Descriptive, statistical analysis will be used to classify the data into two groups, according to the route of administration, while within each group a 3-tiered stratification will be defined by the administered number of doses. The quantitative data will be summarized by estimating the arithmetic mean and median as measures of central tendency, as well as the standard deviation as a measure of dispersion. For qualitative variables, proportions with 95% confidence intervals will be estimated.

After checking the conditions of application and assuming an alpha error of 0.05, the Chi-squared test will be used to determine the statistical differences between the qualitative variables in the two study groups. Prior checking of all the criteria for application will be carried out before the Student’s-t test (0.05 alpha) is used to examine the levels of significance in the differences in quantitative variables for independent data. If the conditions of application were not met, the non-parametric Mann–Whitney U test will be used. The Student’s t test for paired data will be employed for paired quantitative variables.

As an association measurement, relative risk will be estimated with a 95% confidence limit, according to the method of Mantel and Fleiss. In addition, as a further association measurement, relative risk reduction will be calculated with a 95% confidence interval. For the safety study and to control the effect of different confounding covariables, a logistic regression analysis will be simultaneously performed.

As a measurement of impact, the reduction of absolute risk (RAR) and the Number of patients Needed to be Treated (NNT) to prevent an event will be calculated with 95% confidence intervals.

An Intention-to-treat (ITT) analysis will be carried out, even when it was highly or totally improbable that crossing occurs within groups, because this intervention is predictably limited to a particular moment.

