After assessing if the patient fulfilled all inclusion criteria, and none of the exclusion criteria, they were invited to participate in the study and, if they agreed to sign informed consent, were included in one of the tiers, according to the corresponding (allocation ratio 1:1) vaccine dose (one, two or three). The patients were given an appointment to have an INR test and, if the score was less than 4, a blood sample was taken to determine anti-tetanus antibodies, and a dose of vaccine was immediately administered, so that the patient could proceed to the corresponding nursing consultancy. The nurse was responsible for requesting from the randomization centre, by telephone, the administration route to which the patient had been assigned*.* The patient was not informed of the administration route used*.* Patients requiring more than one dose received all doses via the same route, and were given appointments in relation to the interval and number of corresponding doses.

The doctor was blinded to the administration route and also to the follow-up appointments (1, 2, 14 and 30 days) after each dose of the vaccine to detect any side effects.

On the first visit, after administering the vaccine, and at 30 days after the last dose of anti-tetanus vaccine (ATV), the antibody titre was determined for all patients using enzymatic immunoanalysis.

The systematic physical examination at each visit included the following aspects:

 General appearance. Temperature Arterial blood pressure. Measurement of the brachial perimeter at the height of the deltoid on the first visit, and at the site of inoculation after vaccination. Examination and palpation of the injection site looking for basic injuries. Homolateral axillary palpation of the injection site. Any examination required due to the emergence of a general and/or unexpected side effect.

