### Premature abandonment by a patient

The researcher determined the primary reason for premature abandonment by the patient and recorded this information on the CRF. Patients could be prematurely removed from the study for one of the following reasons: side effects in primo-vaccination; patient withdrew consent; loss of follow-up; administrative problems or death.

For patients who could not be contacted and missed the follow-up, the researcher documented the steps taken to contact the patient.

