### Allocation and masking

The randomization unit is the individuals participating in the trial. A random allocation is made within a 3-tiered stratification based on the number of doses of vaccine required for successful immunization (1, 2 or 3 doses). Within each tier, simple randomization is performed by spreadsheet, in an attempt to control the confounder effect of the number of doses.

Mapping is performed by the Fundación Galicia Sur (EOXI Vigo) to which all researchers were given telephone access.

Information concerning the randomization process remained confidential until the end of the study. It is the responsibility of each researcher to ensure that there is a specific procedure that allowed for the opening of the code in case of emergency, with immediate communication to the randomization centre.

The route of administration is masked in the database to prevent the team performing the computer analysis from discovering the route that corresponded to each group.

Loss of masking only occurred in cases of emergency for the patient and at the conclusion of the study.

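### The analysis tiers are defined by doses administered instead of the randomised required-dose tier, and the named between-route tests do not use the tiers

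*Protocol article*

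**What the plan says.** **Randomisation.** Allocation and masking states: "A random allocation is made within a 3-tiered stratification based on the number of doses of vaccine required for successful immunization". It gives the purpose as "in an attempt to control the confounder effect of the number of doses". Under Interventions, the patient is placed in the one-, two- or three-dose tier at inclusion, before the nurse telephones for the route.

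**Analysis.** In Statistical analysis, the sentence that opens with the descriptive analysis says that "within each group a 3-tiered stratification will be defined by the administered number of doses". The Abstract uses the same words.

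**Incomplete courses.** Premature abandonment by a patient lists these reasons for leaving: "side effects in primo-vaccination; patient withdrew consent; loss of follow-up; administrative problems or death".

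**Tests and models.** For qualitative variables, "the Chi-squared test will be used to determine the statistical differences between the qualitative variables in the two study groups". For quantitative variables, Student's t for independent data is planned, with Mann-Whitney as fallback. No tier is named in any of these tests. The same section plans a relative risk by the method of Mantel and Fleiss, without saying what it is stratified by. For safety it adds a logistic regression whose covariables are not listed. The intention-to-treat sentence deals only with crossing between the groups.

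**The concern.** Doses required are a baseline characteristic, so within a required-dose tier the two routes are compared as randomised. Doses administered are observed after randomisation and may depend on the route. A three-dose course spans 7 to 14 months (1–2 months plus 6–12 months), which leaves time for patients to stop. One stated reason for stopping is a side effect, and side effects are the safety outcome. Read literally, a three-dose patient who stops after one dose would be counted with the one-dose patients. That tier would then contain extra patients selected because they reacted, possibly more from one route than the other.

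The same shift would blur tier-level antibody results. Under the vaccination rules in Interventions, one-dose patients have a completed primary course or two earlier doses, while three-dose patients have no known vaccination. An incomplete three-dose patient counted as one-dose belongs to a different population.

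The second issue is efficiency. The trial stratifies in order to control the effect of dose number, yet the named between-route tests do not use that stratification.

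**Working it through.** **1. The plan's own sample size.** Inputs from Sample size: 30% local effects for the intramuscular route, an increase of 18 (read as percentage points, so 48% subcutaneous), two-sided alpha 0.05, beta 0.20. With pooled variance and no continuity correction:

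n = [1.960·√(2·0.39·0.61) + 0.842·√(0.30·0.70 + 0.48·0.52)]² / 0.18² = (1.352 + 0.571)² / 0.0324 ≈ 114.1, rounded up to **115 per group**.

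This matches the stated figure. With 15% loss, 115/0.85 = 135.3, against the stated 135. The calculation has no tier term, so changing the tier definition does not change it.

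**2. How far administered-dose tiers could drift.** Assumptions: the 30% and 48% apply to the first dose, and a common share q of patients with a first-dose reaction stops. The documents give no q. The share of multi-dose patients leaving their randomised tier is q × reaction rate:

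| q (assumed) | Intramuscular | Subcutaneous |
|---|---|---|
| 5% | 1.5% | 2.4% |
| 15% | 4.5% | 7.2% |
| 30% | 9.0% | 14.4% |

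The ratio is 0.48/0.30 = 1.6 whatever q is.

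**3. Effect on a tier-level summary.** Further assumptions: equal tiers of 45 per group (135/3), the same first-dose rates in every tier, and stoppers counted in the one-dose tier. The 90 multi-dose patients per group then include 27 intramuscular and 43.2 subcutaneous first-dose reactors.

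- q = 15%, intramuscular: (13.5 + 4.05)/(45 + 4.05) = 35.8%
- q = 15%, subcutaneous: (21.6 + 6.48)/(45 + 6.48) = 54.5%
- q = 30%, intramuscular: (13.5 + 8.1)/(45 + 8.1) = 40.7%
- q = 30%, subcutaneous: (21.6 + 12.96)/(45 + 12.96) = 59.6%

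The one-dose relative risk moves from 0.48/0.30 = 1.60 to 1.52 (q = 15%) or 1.47 (q = 30%). With required-dose tiers it would stay at 1.60. The overall two-group comparison does not use tier membership, so relabelling tiers leaves it unchanged.

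**4. Cost of leaving the tiers out of the test.** This was simulated with 20,000 runs, 231 patients, three equal tiers, simple randomisation within tier, and an 18-point increase for subcutaneous in every tier. The pooled two-group test was compared with the Mantel-Haenszel statistic, z = Σ(x₂ − n₂m/N) / √Σ[n₁n₂m(N − m)/(N²(N − 1))]. Here, for each tier, x₂ is the number of subcutaneous reactors, n₁ and n₂ the group sizes, m all reactors and N all patients.

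| Intramuscular rates by tier (assumed) | Power, unstratified | Power, stratified |
|---|---|---|
| 30/30/30% | 80.5% | 80.1% |
| 20/30/40% | 80.5% | 81.4% |
| 10/30/50% | 80.8% | 85.1% |

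With no route effect, both tests rejected in 4.9% to 5.0% of runs. Omitting the tiers therefore did not inflate type I error. The power cost is nil when the tiers share one rate and about 4 points when they differ widely.

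**5. Antibody increase.** The documents give no antibody mean or standard deviation by tier, so the gain from adjustment cannot be computed. The adjusted analysis that is named is for safety only.

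**The case against.** The strongest reply is that the administered-dose sentence only classifies data for description, and no test, relative risk or regression is said to use those tiers. The word for administered may also be loose drafting for the assigned tier: the tier is set at inclusion, nothing says that a patient is re-tiered, and patients who stop are described as removed from the study. Both points stand, and they limit the reach of the problem. They do not remove it. Two sections define the tier by a post-randomisation quantity, and route differences within tiers would be read as randomised comparisons.

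A reader might infer that the main safety comparison is biased, or that intention-to-treat is broken. The documents do not support this. All doses go by the same route, so an incomplete course does not change the randomised group, and the overall tests do not involve the tiers.

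A reader might also infer that every between-route analysis ignores the tiers. That too goes beyond the text. A Mantel-type relative risk is normally used for stratified data, and the logistic regression could include the tier. Both are left unspecified, and an unseen analysis plan may settle them. What remains is that the named tests are plain two-group tests and that no adjusted analysis is named for efficacy.

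Finally, an unstratified test is valid here because allocation is 1:1 within each tier. That is correct, so the case for stratifying rests on precision.

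**Conclusion.** The mismatch is real and should be corrected: randomisation uses doses required, while the analysis tiers use doses administered. Its direct effect is confined to tier-level summaries and any route comparison made within tiers. Under the assumed stopping shares, the one-dose relative risk would shift from 1.60 to about 1.5. That illustration also rests on equal tiers, on the plan's rates applying to the first dose, and on a literal reading of the tier definition.

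The unused stratification costs roughly 0 to 4 points of power under assumed tier rates and did not inflate type I error. It matters most for antibody increase, although its size there cannot be derived from the documents. This is a free improvement in analysis, not a bias that must be repaired before the trial's overall comparison can be trusted.

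**What to change.** - In the Abstract and in Statistical analysis, define the analysis tier as the randomised (required-dose) tier instead of by doses administered.
- For the binary safety comparison, use a Cochran-Mantel-Haenszel test over the randomised tiers. Report the Mantel-Haenszel pooled relative risk and risk difference with 95% confidence intervals, and derive the number needed to treat from that risk difference.
- Include the randomised tier as a factor in the logistic regression and in the model for antibody increase.

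The cost is wording and analysis code only. The tier is already recorded at inclusion, and the sample size does not change.

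### Brachial perimeter, a main safety variable, has no stated baseline-adjusted comparison between routes, so precision is given up although a first-visit perimeter is collected

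*Protocol article*

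**What the plan says.** All references are to the protocol article, Methods/design.

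- **Variables.** The first main safety variable is "Measurement of the brachial perimeter in centimetres". It is worded as a level. The efficacy variable in the same section is worded as an increase. Redness, swelling, heat, granulomas and haematoma at the injection site are listed separately as further main safety variables.
- **Interventions.** The examination at each visit includes "Measurement of the brachial perimeter at the height of the deltoid on the first visit, and at the site of inoculation after vaccination". There are "follow-up appointments (1, 2, 14 and 30 days) after each dose of the vaccine to detect any side effects", and a patient may need one, two or three doses.
- **Statistical analysis.** For quantitative variables, the Student's t test "is used to examine the levels of significance in the differences in quantitative variables for independent data"; if its conditions fail, "the non-parametric Mann–Whitney U test will be used". The section adds: "The Student’s t test for paired data will be employed for paired quantitative variables". The one adjusted model is this: "For the safety study and to control the effect of different confounding covariables, a logistic regression analysis will be simultaneously performed". Perimeter is not mentioned by name anywhere in the section.

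**The concern.** A perimeter taken after vaccination probably reflects mainly how large the patient's arm is. An independent-samples test on that value leaves between-person arm size in the error term, although a first-visit measurement that could remove much of it is already on the case report form.

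The other listed methods do not close the gap. A paired t test asks whether perimeter changed within patients; it does not estimate the intramuscular (IM) minus subcutaneous (SC) difference. Logistic regression does not take an outcome in centimetres.

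The point matters because bleeding after IM injection is the harm that motivates the trial (Background), and the Discussion hopes to support routine IM use on the ground that it is safe. Low precision on a main safety variable makes a non-significant result more likely, and here such a result would tend to be read as reassuring.

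**Working it through.** **1. The plan's own sample size.** It rests on a binary endpoint (Sample size section): 30% local effects with IM, an 18-point increase to 48% with SC, two-sided 0.05, power 80%. With pooled variance and mean proportion 0.39:

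n = [1.960 × √(2 × 0.39 × 0.61) + 0.842 × √(0.30 × 0.70 + 0.48 × 0.52)]² / 0.18² = 114.1, so 115 per group, as stated.

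Allowing for 15% loss, 115 / 0.85 = 135.3, against 135 stated. The figure is reproduced. It was not derived for perimeter.

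**2. Inputs for perimeter.** From the article: 115 analysed per group, 1:1 allocation, alpha 0.05. I take the test as two-sided, as in the sample size, and use 80% power. The article gives neither the SD of perimeter nor the correlation ρ between first-visit and later values, so both are assumptions. Results are shown first in SD units and then for an illustrative SD of 3 cm.

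**3. Effective SD under each analysis** (equal variances before and after):

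- raw post-vaccination value: SD
- change score: SD × √(2(1 − ρ))
- ANCOVA on baseline: SD × √(1 − ρ²)

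**4. Detectable difference.** The noncentral t distribution with 228 degrees of freedom gives 0.371 SD for the raw test. (The normal approximation, 2.80 × √(2/115), gives 0.369.) Multiplying 0.371 by the factors above:

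| ρ (assumed) | Raw | Change score | ANCOVA |
|---|---|---|---|
| 0.5 | 0.371 SD | 0.371 SD | 0.321 SD |
| 0.8 | 0.371 SD | 0.235 SD | 0.223 SD |
| 0.9 | 0.371 SD | 0.166 SD | 0.162 SD |

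**5. Illustration in centimetres.** With SD 3 cm, the raw test has 80% power for 0.371 × 3 = 1.11 cm. For a true route difference of 0.5 cm (0.5 / 3 = 0.167 SD), power is:

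| ρ (assumed) | Raw | Change score | ANCOVA |
|---|---|---|---|
| 0.5 | 24% | 24% | 31% |
| 0.8 | 24% | 51% | 55% |
| 0.9 | 24% | 80% | 82% |

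If the SD were between 2 and 5 cm, the raw detectable difference would run from about 0.74 cm (0.371 × 2) to about 1.86 cm (0.371 × 5).

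**6. Reading the tables.** ANCOVA is at least as precise as the raw test at every ρ, apart from the few degrees of freedom it uses. A change score improves on the raw test only when ρ exceeds 0.5.

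**The case against.** **The Statistical analysis section is a generic list and never names perimeter.** A change in centimetres is itself a quantitative variable for independent groups, so a t test on changes fits the wording, and the wording of the Variables section may only state what is measured and in which unit. This stands. The contrast with the antibody increase favours the raw reading but does not prove it. If changes were intended and ρ is near 0.9, almost nothing is lost (80% against 82% power in the illustration). At ρ 0.5 a change score gains nothing.

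**An article condenses the full protocol, and an analysis plan is not shown.** True, and silence on covariates alone would be no finding. Here, however, the article states both the variable and the family of between-route tests, and together they leave out a baseline that the trial collects.

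**The unadjusted comparison is valid.** It is. Under randomisation it is unbiased. A reader might infer that chance imbalance in arm size is a further harm; it is ordinary sampling error, already reflected in the test and in any confidence interval.

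**A swelling or haematoma signal would be hidden.** A reader might infer this, but the document does not support it. Both signs are found by examination and palpation and recorded in their own right, and the plan provides a chi-squared test, relative risk and logistic regression for outcomes of that kind. A null on perimeter cannot be called likely either, since no SD, correlation or relevant difference is given; under the same assumed SD of 3 cm, the raw test has 80% power at about 1.1 cm.

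**The two perimeters may not be the same measurement.** The first is described at deltoid height, the later ones at the inoculation site. If these levels differ, ρ could be lower and a subtraction hard to interpret. This stands, and must be settled before any baseline adjustment.

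**Conclusion.** The point holds as a matter of precision on one main safety variable. The only between-route methods stated for quantitative data are unadjusted, and no section uses the first-visit perimeter to compare routes.

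If the raw value is analysed, the detectable difference at 115 per group is 0.371 SD, where ANCOVA would reach 0.321 to 0.162 SD for ρ from 0.5 to 0.9. That is a reduction of 13% to 56% (1 − √(1 − ρ²)). The gain is modest at the low end and large at the high end. Its size depends on an assumed ρ, and any figure in centimetres also on an assumed SD. If change scores were meant, most of the gain is already secured at high ρ.

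The documents do not support a claim of bias, or of a bleeding signal lost to the trial as a whole.

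**What to change.** 1. Confirm that first-visit and follow-up perimeters are measured at the same level of the arm, and say so in the definition.
2. Compare routes by ANCOVA: post-vaccination perimeter at one prespecified early visit after the first dose, on route, pre-vaccination perimeter and randomised dose tier. A repeated-measures model over the scheduled visits, with the same adjustments, is an alternative. Either way, the visit and dose must be named, since there are four visits after each of up to three doses.
3. Report the adjusted IM minus SC difference in cm with its 95% CI, so that a non-significant result shows which differences remain compatible with the data.
4. Keep the paired t test as a within-arm description only.

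Cost: revised analysis wording, one regression model, a few degrees of freedom, and a simple rule for patients without a baseline perimeter. No new patients or measurements are needed, provided the arm level proves consistent.
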